**Fig. 1 Fig1:**
[figure not shown]
Study flowchart - recruitment and randomisation

### Assessments

#### Qualitative data

We will record dropouts and the reasons for dropouts. We will record patients’ subjective opinions on hypnosis, VR and VRH, collected through an interview. We also record the nurses’ opinions on hypnosis, VR and VRH collected through an interview about the applicability and the usability of the tools.

#### Demographic factors

We will collect data on age and gender, duration of surgery and type of cardiac surgery (aortic valve replacement, mitral valve replacement or coronary artery bypass surgery). Patients in the ICU are not currently consuming alcohol, but their treatment can be influenced by their previous daily alcohol consumption. The investigator will therefore ask patients about their habitual alcohol and social drug consumption per day and per week. Tobacco withdrawal symptoms (e.g. nervous behaviour) could also influence the participant’s behaviour on the postoperative day. The investigator will therefore ask patients whether they are smokers (yes/no).

#### Psychological outcomes

Anxiety, pain, relaxation and fatigue will be evaluated using a VAS before and after the 20-min sessions. The VAS score helps to determine the intensity of these psychological variables, as subjectively assessed by the patient, on a scale ranging from 0 to 10. The daily dissociative profile will be assessed using the Dissociative Experience Scale (DES) 28-items [58].

Absorption is the “tendency to become fully involved in a perceptual, imaginative, or ideational experience” [59, 60]. We asked subjects to answer this question: “Could you estimate on a 0- (not at all) to 10- (fully) scale how deeply you felt absorbed and felt your attention as focalized and focused by the experience you have just lived?” [60].

Dissociation: is “a mental separation of components of experience that would ordinarily be processed together” [24, 60]. We asked subjects to answer this question: “Could you estimate on a 0-to-10 scale if you felt a dissociation between your bodily sensation and the actual environment? Zero means you were in the reality, in this room; 10 means that you completely escaped in your subjective experience, totally disconnected from the here-and-now reality” [60].

Immersion and presence will be assessed using a VAS. The questions will be “From 0 to 10, how much did you feel present in the environment?” and “From 0 to 10, how much did you really feel the sensations suggested by the therapist?”

Time perception: we will ask subjects to estimate the time elapsed in minutes since they started the session. Time perception will be calculated as the absolute value of the real duration of the experience (hypnosis, VR, VRH) minus the subjects’ estimated duration [60]. The experimenter will record the start and end times of the session.

#### Physiological outcomes

We will assess heart rate: normal heart rate is from 60 to 110 heart beats per minute (depending on whether or not the patient regularly pratices sport) [61]; arterial pressure: normal arterial pressure is from 9.5 to 14.9 [62]; respiratory rate: normal respiratory rate is from 12 to 20 cycles per minute [61]; oxygen saturation: normal values of oxygen saturation are from 95% to 100% [61]; and pupil size: pupil diameter varies from 1 to 10 mm and normal range is from 2 to 8 mm [63].

### Data coding and storage

Data encoding will be assured by the principal investigator of the study (FR). Data will be stored on DOXUlg (https://dox.uliege.be). DOXUlg is a platform for the University of Liège that is secure and confidential. Patients’ data will be accessible only to the principal investigator and promotor to maintain the confidentiality of data.

### Statistical analysis

Normality will be investigated graphically by histogram and quantile-quantile plot and tested using the Shapiro-Wilk test. Continuous variables will be reported as mean (plus/minus standard deviation) or median (interquartile range) for skewed distributions, and qualitative variables as number and percentage. Homogeneity of the four groups will be assessed using the chi-squared test for qualitative and dichotomous variables and one-way (ANOVA-1) or the non-parametric Kruskal-Wallis test for quantitative variables. Repeated measures ANOVA will be used to compare the evolution of the parameters between day − 1 and day + 1 morning and afternoon, according to the groups. This analysis will be adjusted by the potential confounding factors. Calculations are always carried out on the maximum number of data available. Results will be considered as statistically significant at the 5% critical level (*p* < 0.05). Analyses will be performed using R 3.5.3 (R Core Team) and the package Rcommander (Rcmdr) and using SAS 9.4 (© SAS Institute Inc., Cary, NC, USA) [64].

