## Methods/design

### Aim

The aim of the project is to better understand the impact of VR, hypnosis and VRH on individual perception and sensation in patients hospitalized in cardiac surgery and ICU departments. The primary outcome will be patients’ anxiety levels preoperatively and in postoperative recovery. Secondary assessments will include assessment of pain, fatigue, relaxation, physiological parameters, absorption, dissociation and presence concepts.

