In VRH, we replace the sounds of nature used for the VR device by the hypnotic tape in order to have the ideal experimental conditions to compare the techniques. The *Soothing white clouds* hypnosis session is combined with a 3D visual movie (immersive landscape and relaxing moment in the clouds (Oncomfort©)), with a duration of 20 min. The text for hypnosis is the same as in the hypnosis group and includes suggestions about relaxation, positive body sensations, invitation to observe a sunrise and a beautiful landscape, while relaxing in a white cloud chair. The hypnosis script was previously recorded (see hypnosis group description) and then integrated into the VR device. In that way, participants can listen to the hypnosis record throughout the VR session.

Initial contact between the investigator and the patient will take place in the patient’s room one day before cardiac surgery. The investigator will request each patient to consent for participation in the study and subsequently record their demographic data (age, gender, surgery type, alcohol and tobacco use). Hypnosis, VR or VRH will be applied in 20 min session: the day before surgery (day − 1 at 5.00 p.m.) and the day after surgery (day + 1 at 2.00 p.m.). Before and after each session, physiological measurements will be recorded (heartbeat, arterial pressure), and a visual analogical scale (VAS) will be used to assess anxiety, fatigue, pain and relaxation. The VAS is a continuous scale subjectively assessed by the patient and ranges from 0 (no pain/anxiety/fatigue/relaxation) to 10 (maximum pain/anxiety/fatigue/relaxation). We ask the patients to assess their “current pain intensity/anxiety/fatigue/relaxation at the moment”. This score determines the intensity of these variables at a given time [57]. After the session, patients will complete questions about absorption and dissociation (Table 2).

**Table 2 Tab2:** Standard Protocol Items: Recommendation for Interventional Trials (SPIRIT) study schedule

Timepoint	Study period				
	Hospital admission (Day − 1)		Surgery (Day 0)	Intensive care unit admission (Day + 1)	
	***T0***	***T1***		***T2***	***T3***

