**Assessments**					
**Baseline:** demographic factors, Dissociative Experience Scale [58]	**X**				
**Primary outcome:** anxiety	**X**	**X**		**X**	**X**
**Secondary variables**: pain, fatigue, relaxation, heart rate, arterial pressure, respiratory rate, oxygen saturation, pupil size	**X**	**X**		**X**	**X**
**Phenomenology scales**: absorption, dissociation, immersion, presence, time perception		**X**			**X**
Nurse’s and patient’s interview		**X**			**X**

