### Recruitment and randomisation

Each patient scheduled for cardiac surgery who meets our exclusion and inclusion criteria will be asked to participate. The number of patients who refuse to participate will be recorded, and demographic data will be collected to allow a comparison with those who participate. Written informed consent will be obtained before inclusion. The selected patients will be randomly assigned to one of the four groups, using block randomisation with a block size of 5 to obtain a good balance of participants between the four groups during the recruitment period. The recruitment started in October 2018 and is ongoing. Sample size has been determined by a power analysis calculated to detect a difference in the evolution of data between the four groups. The sample size calculation was based on repeated measures analysis of variance (ANOVA). Alpha was set at 0.05, power at 95% and the standardized effect size at 0.5. In other studies designed to assess the effect of hypnosis on patients’ anxiety pre-surgery, an effect size of 0.2 has been considered small, 0.5 moderate and 0.8 large [29]. According to this analysis, 12 patients are required in each group giving a total of 48 patients. We decided to enrol 100 patients (25 per group) at day 1 to compensate for dropouts on the day after surgery (Fig. 1).

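### The only outcome analysis names a day +1 morning assessment that the schedule does not contain, and its possible readings give different answers

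*Protocol article*

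**What the plan says.** The protocol article's Statistical analysis section describes a single inferential analysis of the outcomes: a repeated measures ANOVA, adjusted for potential confounders, to "compare the evolution of the parameters between day − 1 and day + 1 morning and afternoon, according to the groups". It labels no analysis as primary, but gives no other for anxiety.

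The timing is set out elsewhere in the article:

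- **Design:** sessions take place "the day before surgery (day − 1 at 5.00 p.m.) and the day after surgery (day + 1 at 2.00 p.m".
- **Design, on measurement:** "Before and after each session, physiological measurements will be recorded (heartbeat, arterial pressure), and a visual analogical scale (VAS) will be used to assess anxiety".
- **Psychological outcomes:** "Anxiety, pain, relaxation and fatigue will be evaluated using a VAS before and after the 20-min sessions".
- **SPIRIT schedule (Table 2):** the row "Primary outcome: anxiety" is marked at T0 and T1 on day −1 and at T2 and T3 on day +1.
- **Aim:** "The primary outcome will be patients’ anxiety levels preoperatively and in postoperative recovery". The two periods are not ranked.

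**The concern.** The analysis sentence and the schedule describe different data. The sentence has one undivided day −1 and a day +1 split into morning and afternoon. The schedule has two before/after pairs, both in the afternoon. An analyst must decide what day −1 stands for and what takes the place of the morning value, and the text does not settle either.

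The choice affects the result. The aim covers anxiety before surgery and in recovery, and each session is bracketed by ratings so that its effect can be seen. Some readings of the sentence discard or cancel that effect. If the choice is made after the data are seen, the reported contrast can follow the result. The sample size in Recruitment and randomisation rests on a difference between the four groups in the evolution of the data, so the same vagueness carries over to what the stated 48 patients are meant to detect.

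**Working it through.** **1. The wording against the schedule**

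| | Statistical analysis | Schedule (Design, Table 2) |
|---|---|---|
| Day −1 | one occasion | T0 before and T1 after the 5 p.m. session |
| Day +1 | morning, afternoon | T2 before and T3 after the 2 p.m. session |
| Total | 3 | 4 |

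No section schedules a morning rating on either day.

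**2. What the readings estimate**

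For illustration, let an active arm differ from control by 0, −0.5, 0, −0.5 at T0, T1, T2, T3: the same session effect on both days and no carry-over. The size and pattern are assumptions.

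- *T0 with T2 and T3:* the differences used are 0, 0, −0.5. T1 is absent, so nothing is learned about the preoperative session beyond any carry-over to T2.
- *Day mean against day mean:* day −1 gives (0 − 0.5)/2 = −0.25 and day +1 gives (0 − 0.5)/2 = −0.25. The change is −0.25 − (−0.25) = 0. In general δ/2 − δ/2 = 0 for any equal session effect δ, so an intervention that works on both days shows no group difference in evolution.
- *All four occasions:* the interaction has (4 − 1)(4 − 1) = 9 degrees of freedom and contains both before/after contrasts. A significant result does not say at which occasion, or in which arm, the effect lies.

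**3. Does the stated sample size reveal the intended occasions?**

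The plan gives "Alpha was set at 0.05, power at 95% and the standardized effect size at 0.5" and 12 per group, 48 in total. It states neither the number of measures m nor the correlation ρ. Take 0.5 as Cohen's f and ρ = 0.5 (both assumptions). For the between-groups effect, λ = N·m·f²/(1 + (m − 1)ρ) with N − 4 error degrees of freedom:

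- m = 4: λ = 48·4·0.25/2.5 = 19.2, power 0.954, so N = 48 is reproduced.
- m = 3: λ = 48·3·0.25/2 = 18.0, power 0.941, so N = 52 is needed.
- m = 2: λ = 48·2·0.25/1.5 = 16.0, power 0.910, so N = 56 is needed.

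N = 48 also results from m = 3 with ρ = 0.4 and from m = 2 with ρ = 0.2. The figure fits four occasions but does not prove that they were meant.

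**4. Power of the candidate tests**

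Assume d = 0.5 in all three active arms at T1 and T3, nothing at T0 and T2, and ρ = 0.5. The variance of the group means (0, 0.5, 0.5, 0.5) is 0.046875.

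- *Interaction over T0–T3:* f² = 0.046875 × 0.25 = 0.0117 (f = 0.108), λ = 4N·f²/(1 − ρ). N = 48: λ = 4.5, df 9 and 132, power 0.238. N = 100: λ = 9.375, df 9 and 288, power 0.516.
- *T1 adjusted for T0:* λ = 0.046875·N/(1 − ρ²). N = 48: λ = 3.0, df 3 and 43, power 0.253. N = 100: λ = 6.25, df 3 and 95, power 0.518.
- *Change from T0 to T1, N = 100:* λ = 4.6875/[2(1 − ρ)] = 4.6875, df 3 and 96, power 0.400.

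At equal N the first two tests have practically the same power. Adjusting for baseline beats the change score.

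**The case against.** The strongest defence is that the wording is a slip. Day −1 contains T0 and T1, and a repeated measures ANOVA over all scheduled occasions would include both before/after contrasts. A condensed article may leave contrasts, their order and the division of alpha to a fuller plan. This stands in part. T0 to T1 is unnamed, not excluded, and failing to name contrasts would not by itself be a finding. But a statement that conflicts with the schedule is more than an omission. Reading morning as T2 and afternoon as T3 does not repair it, because day −1 would still be one occasion where the schedule has two.

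Three stronger inferences are tempting, and the document does not support them:

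- *The omnibus test wastes power on its degrees of freedom.* At equal N it does not (0.238 against 0.253; 0.516 against 0.518). A large gap appears only if the interaction is given 48 patients and the T1 test 100. The document does not forecast 48 completers: that is the calculated requirement. Nor does it restrict the analysis to complete cases, since it says that all available data are used.
- *The plan leaves T0 to T1 out.* Only some readings do.
- *Surgery, sedation and analgesia distort the comparison.* A shift common to all arms goes into the time effect. It can add noise but does not bias a randomised group-by-time comparison.

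**Conclusion.** The contradiction stands. The article's only outcome analysis refers to an assessment that the schedule does not contain, so it cannot be carried out on the scheduled data as worded. The error is best measured by what the readings return for the same truth. With a session effect of −0.5 on both days, a day-mean comparison gives 0, a T0/T2/T3 analysis shows only the postoperative half, and a four-occasion model holds both effects without naming either. The exact cancellation assumes equal effects and no carry-over at T2; otherwise it is partial. No bias or loss of power can be attached to the sentence, because it does not fix one test. The power figures rest on the assumed d, ρ and pattern, and serve only to compare tests. The contradiction itself needs no assumption, and it should be resolved before the outcome data are analysed.

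**What to change.** Replace the sentence in Statistical analysis:

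- Delete the morning/afternoon wording and refer to T0–T3 as in Table 2.
- Use one likelihood-based repeated-measures model for anxiety at T1, T2 and T3 on all available data, with group, occasion, their interaction and T0 anxiety as baseline. Preoperative ratings of patients who drop out after surgery are then kept.
- Name the group comparisons at T1 and at T3 as the primary contrasts. Because the Aim, "anxiety levels preoperatively and in postoperative recovery", does not rank them, either test them in a stated fixed order or test each at 2.5%.
- Report T2 for carry-over. Do not use it as the baseline for T3, because it is measured after session 1 and may already reflect treatment.

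No new data are needed; the cost is wording. The downside is that in a fixed order the T3 claim depends on T1. With split alpha each test loses some power: for T1 adjusted for T0, λ = 6.25 with df 3 and 95 gives 0.518 at 5% and 0.403 at 2.5%, under the same assumed d = 0.5 and ρ = 0.5 with 100 patients.

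### Pre-treatment (T0) anxiety appears to be analysed as a level of the outcome; using it as a covariate would raise power at almost no cost

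*Protocol article*

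**What the plan says.** The SPIRIT schedule (Protocol article, Table 2) marks anxiety, the primary outcome, at T0, T1, T2 and T3. T0 and T1 fall before and after the session on the day before surgery; T2 and T3 fall before and after the session on the day after surgery. The separate baseline row holds only demographic factors and the Dissociative Experience Scale.

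The Statistical analysis section compares the course of each parameter from day −1 to day +1 between groups by repeated measures ANOVA. It does not list the levels of the time factor as T0 to T3. On adjustment it says "This analysis will be adjusted by the potential confounding factors". Earlier in the same paragraph it plans baseline tests: "Homogeneity of the four groups will be assessed using the chi-squared test for qualitative and dichotomous variables", with ANOVA or Kruskal-Wallis for quantitative variables.

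Under Recruitment and randomisation, "The sample size calculation was based on repeated measures analysis of variance (ANOVA"), with these inputs: "Alpha was set at 0.05, power at 95% and the standardized effect size at 0.5". The result is "12 patients are required in each group giving a total of 48 patients", raised to 100 to allow for dropout. No correlation between time points is given.

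**The concern.** T0 is measured before any session, so under randomisation the four arms have the same expected T0 anxiety. If T0 is one of four outcome levels, a group-by-time test in effect works with changes from T0, and these carry the full noise of the T0 measurement. With T0 as a covariate, only the part of T0 that predicts later anxiety is removed. The covariate analysis is the more precise whenever the correlation is below 1.

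What is at stake is precision in a small trial: 25 patients per arm enrolled, and possibly as few as the calculated 12 per arm completing day +1. The T0 values are already collected.

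A second, smaller issue is the wording about confounders. In a randomised trial, baseline differences between arms arise by chance, so tests of homogeneity cannot identify confounders. The text gives no rule that would prevent covariates from being chosen after looking at such differences.

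**Working it through.** **1. The plan's own figure.** Inputs from the protocol article: four groups, alpha 0.05, power 95%, effect size 0.5. Assumed here: 0.5 is Cohen's f, there are four times, and the correlation rho is 0.5. For the between-group effect in repeated measures ANOVA:

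λ = f²·N·m / (1 + (m−1)·rho) = 0.25 × 48 × 4 / 2.5 = 19.2, with df 3 and 44, gives power 0.954.

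N = 44 gives 0.933, so 12 per group (48 in total) is reproduced. Neither the correlation nor the effect metric is stated, so both must be assumed in what follows.

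**2. One between-arm contrast at T1.** In units of the outcome variance, with correlation rho between T0 and T1:

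- change from T0: 2(1 − rho)
- T0 as covariate: 1 − rho²
- ratio: (1 + rho)/2

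| rho | change | T0-adjusted | reduction |
|---|---|---|---|
| 0.3 | 1.40 | 0.91 | 35% |
| 0.5 | 1.00 | 0.75 | 25% |
| 0.7 | 0.60 | 0.51 | 15% |

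**3. Like-for-like omnibus test.** Both analyses use 9 df, and only the role of T0 changes. With T0 as a level, the test is the group-by-time interaction over four times (3 × 3 = 9 df). With T0 as a covariate, it is the joint test of group differences at T1, T2 and T3 (also 3 × 3 = 9 df).

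Assumptions: compound symmetry, n = 25 per arm, and a shift of d = 0.5 SD in the three active arms. The between-group sum of squares is s = 0.75 × 25 × 0.5² = 4.6875. Let v mark the times with an effect, k be the number of such times, I the identity matrix and J the matrix of ones.

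- T0 as level: covariance of the three changes (1 − rho)(I + J), so λ = s·(k − k²/4)/(1 − rho)
- T0 as covariate: covariance (1 − rho)(I + rho·J), so λ = s·(k − k²·rho/(1 + 3·rho))/(1 − rho)

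For an effect at T1 and T3 (k = 2) and rho = 0.5:

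- level: 4.6875 × (2 − 1)/0.5 = 9.375, power 0.516
- covariate: 4.6875 × (2 − 0.8)/0.5 = 11.25, power 0.611

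Power, T0 as level → T0 as covariate:

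| effect at | rho 0.3 | rho 0.5 | rho 0.7 |
|---|---|---|---|
| T1, T2 and T3 | 0.274 → 0.578 | 0.387 → 0.611 | 0.633 → 0.768 |
| T1 and T3 | 0.368 → 0.505 | 0.516 → 0.611 | 0.785 → 0.829 |
| T1 only | 0.274 → 0.308 | 0.387 → 0.413 | 0.633 → 0.650 |

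The gain runs from 1.7 points (T1 only, rho 0.7) to 30.4 points (sustained effect, rho 0.3). It is positive in every cell. With 12 per arm and rho 0.5, the three rows become 0.182 → 0.285, 0.238 → 0.285 and 0.182 → 0.192.

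**4. Cost.** The error df fall from 288 to 287 with one common T0 slope, or to 285 with one slope per time point. The powers above are unchanged to within 0.001.

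**The case against.** **The size of the gain rests on inputs the article does not give.** This stands. If the planned 0.5 is Cohen's f, a one-time-point four-group test at N = 100 and rho 0.5 already has power 0.991 and could rise only to 0.999. If the effect appears only at T1, the gain is 2 to 3 points. The direction of the gain does not depend on these inputs in the settings run; its size does.

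**A reader might expect a larger gain by also reducing the test to 3 df on the mean of T1 and T3.** With the effect at both times and rho 0.5, power is then 0.711 against 0.516. That step is not due to T0 adjustment. The noncentrality is 9.375 in both tests, and a 3-df contrast of the mean of T1 and T3 minus the mean of T0 and T2, without a T0 covariate, also gives 0.711. If the effect is only at T1, averaging drops power to 0.21 against 0.39 for the 9-df interaction.

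**A reader might infer that the homogeneity tests select the covariates.** The text does not say so. The two sentences are not linked, and the Demographic factors section gives subject-matter reasons for recording alcohol and tobacco use. What stands is that selection by these tests is not excluded.

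**A reader might also infer that duration of surgery is a planned covariate.** That section says only "We will collect data on age and gender, duration of surgery and type of cardiac surgery"; collecting a variable is not a plan to adjust for it.

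**The article is condensed.** A covariate list, and the exact levels of the ANOVA, may be in an analysis plan that is not shown. The absence of a list is therefore no finding. The point rests on the listing of T0 as an outcome time and on the model that is named.

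**Conclusion.** The point holds as an efficiency improvement, not as an error that invalidates the analysis. On the natural reading of Table 2 and the Statistical analysis section, T0 anxiety is an outcome level and not a covariate.

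Moving it cuts the variance of a T1 contrast by 35% to 15% relative to change from T0, for correlations of 0.3 to 0.7. It adds about 2 to 30 points of power in a 9-df test with 25 per arm and a 0.5 SD shift. These figures assume compound symmetry, equal shifts in the three active arms and complete data; the correlation, shift and effect patterns are all assumptions.

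The documents do not support saying that data-driven covariate selection or adjustment for surgery duration is planned.

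**What to change.** - State that T0 anxiety is a covariate and that the outcome vector is T1, T2 and T3. Equivalently, keep T0 in the model with its mean constrained to be equal across arms.
- Name the test as the joint comparison of groups over T1 to T3. A group-by-time interaction restricted to those three times has only 6 df and would miss a constant shift.
- Treat each secondary outcome measured at T0 (pain, fatigue, relaxation and the physiological measures) in the same way with its own T0 value. The phenomenology scales are not scheduled at T0, so this does not apply to them.
- Replace the sentence on confounders with a rule: any further covariate is a pre-randomisation factor chosen in advance. Describe the arms at baseline without using homogeneity tests to decide on adjustment.

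The cost is a change of wording and about one degree of freedom per time point. T0 is scheduled before surgery, so few values should be missing, and no additional data are needed.
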